#### Visit 4 (week 6)

Marks the end of doing acupressure and the beginning of the follow-up phase: Participants complete a battery of questionnaires, are asked about any adverse events, assessed for blinding, and tested for acupressure fidelity (see Table
2). Data from the Actiwatch-S are downloaded and the reinitialized and a14-day sleep diary is given to them. If the participant belongs to the acupressure treatment arm of the study they are asked to stop acupressure treatment for the next 4 weeks.

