### Study measures

#### Subjective study measures

Below is a list of self-report measures that participants complete per the schedule in Table
2.

*Hospital Anxiety Depression Scale):* this 15-item questionnaire is a widely used instrument to measure depression and anxiety
[15].

*Primary Care Evaluation of Mental Disorders (PRIME-MD):* It is a 26-item self-administered questionnaire that screens for five of the most common groups of psychiatric disorders in primary care: depression, anxiety, alcohol, somatoform and eating disorders
[16].

*Brief Fatigue Inventory:* The BFI assesses the severity of fatigue and the impact of fatigue on daily functioning in patients with fatigue due to cancer and cancer treatment
[17].

*Actiwatch-S to collect fatigue severity:* Four times daily participants indicate on a scale from 0 = “No Fatigue” to 10 = “Extremely Fatigued,” their fatigue severity at that moment. These scores are entered into the Actiwatch-S upon completion of their acupressure treatment and at three pre-scheduled times, once in the morning (9:00 AM), once in the afternoon (3:00 PM) and once in the evening (9:00 PM).

*Long Term Quality of Life Instrument:* The LTQL is a 34 items questionnaire that is self-administered for evaluating functional impairment and the perceived effect of that impairment on quality of life in breast cancer survivors
[18].

*Breast and Surrounding Area Pain Questionnaire:* The BSAPQ is used for measuring pain in the area of the breast (defined as the breast, armpit, side of the body, or arm on the operated side) on either the operated breast or the area from which the breast was removed
[19].

*Brief Pain Inventory:* The BPI is used to assess average clinical pain
[20].

*General Self-Efficacy Scale:* The construct of Perceived Self-Efficacy reflects an optimistic self-belief that one can perform a novel or difficult task, or cope with adversity in various domains of human functioning
[21].

*Pittsburgh Sleep Quality Index:* The PSQI evaluates sleep disturbance over the past month.
[22]. *Sleep Diary:* Sleep diaries are simple, non-invasive, self-report measures that provide night-to-night information on sleep pattern, quality, and relevant daytime behavior.

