## Statistical issues

### Statistics and power analysis

Primary Aim: The primary aim of this study is to investigate the differential effects of different modes of acupressure on fatigue in breast cancer survivors. For this, we are focusing on three fatigue outcomes, namely, BFI, which will be administered weekly, a measure of average daily physical activity and a self-reported fatigue score, both based on Actiwatch-S data. A BFI is collected weekly and provides a measure of average degree of fatigue, a score that ranges between 0 and 10, with higher numbers indicating more fatigue. We will be analyzing the BFI outcome over phases. The first phase BFI is obtained by averaging week-1 to week-3 measures (mid-treatment). The second phase comprising of week-4 to week-6 measures indicates the status in the second half of the treatment phase (end-treatment). The final phase comprises of week-7 to week-10, the washout phase (washout). In order to investigate the change in BFI between the three study arms, we are using a mixed-effects regression analysis with average BFI in the three phases as the outcome, phase as the within-subjects factor, and group (RA, SA, standard of care) as the primary between-subjects factor. The baseline BFI level will be used as a covariate. We shall further adjust the model for key demographic variables such as age and ethnicity, as well as the baseline HADS score. A *subject* random-effect will be used to account for the clustering effect within the three measurements on the same subject. Of primary interest is the group*phase interaction, the significance of which will indicate differences in extent of decrease between the arms. Post-hoc analyses of phase difference within each arm will be carried out multiple comparison adjustment. Model diagnostics will be carried out to confirm the distributional assumptions and appropriate corrective actions (e.g. transformation) will be performed as needed.

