One of the most widely used sleep measures is the PSQI, which shall be administered at baseline, week 6 and week 10. We shall follow the scoring convention followed for PSQI which constructs scores for seven components, namely sleep quality; sleep latency; sleep duration; habitual sleep efficiency; sleep disturbances; use of sleep-promoting medication; and daytime dysfunction, all derived from the original PSQI. The component scores are summed to obtain a total score, the primary outcome for the proposed study. The modeling framework and subsequent analysis will be similar to that for BFI with the phase variable replaced by a continuous week variable. A logistic regression analysis will be carried out with a dichotomous outcome indicating whether PSQI > 7 or not since the threshold of 7 is considered an indicator for sleep quality in BC survivors. A number of secondary sleep outcomes will be obtained using a conjunction of the Actiwatch-S-S data and sleep diary. These will include measures of total sleep time (minutes spent asleep each night) and sleep efficiency (total sleep time/time in bed* 100). These can all be analyzed using the models and methods described above within the mixed linear or logistic regression modeling framework as appropriate.

2. Assessing differences in time to onset and time to relapse (after treatment ends) across the acupressure arms

Time to onset of the acupressure effect will be investigated by studying the treatment subgroups, namely RA and SA. For fatigue, we shall use the daily average values of VAS-F. Time to onset will be calculated as the first time (in days) the VAS falls down by 3 points in comparison to the baseline. We shall restrict this analyses to subjects whose baseline VAS-F is at least 3. A proportional hazards regression model will be employed to analyze the time to onset data. Treatment arm (RA vs. SA) will be used as the primary covariate in the analysis. Independent variables used in the earlier regression analyses for the primary and secondary aim 1 will be used as additional covariates.

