[33]. The mean PSQI values at mid-treatment are assumed to be 7, 6, 6, respectively in standard care, SA and RA arms whereas the means are taken to be 7, 6, 5 at the end-treatment point in the same arms. Assuming an intra-subject correlation of 0.5, we have powers above 99% to detect any of the group, phase, and group*phase interaction effects with a sample size of 100 per treatment arm and a 5% level of significance.

All power calculations are carried out on the basis of 100 simulations in the software PASS 2008 (NCSS, Kaysville, Utah, USA).

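### The PSQI test inherited from the BFI model, group by continuous week, does not estimate the effect of six weeks of acupressure on sleep; the week-6 contrasts between arms should be the target

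*Protocol article*

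**What the plan says.** All references are to the protocol article.

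- **Aim.** Study aims and hypotheses sets the sleep aim as the effect of six weeks of RA against SA or standard of care. The PSQI total is the lead outcome of that aim.
- **PSQI model.** Statistics and power analysis, first secondary aim: "The modeling framework and subsequent analysis will be similar to that for BFI with the phase variable replaced by a continuous week variable".
- **PSQI times.** The same paragraph describes the PSQI as an instrument "which shall be administered at baseline, week 6 and week 10". Table 2 places the first PSQI at the screening visit and has none at week 3.
- **The framework carried over.** For the BFI, "The baseline BFI level will be used as a covariate", and "Of primary interest is the group*phase interaction, the significance of which will indicate differences in extent of decrease between the arms".
- **Treatment timing.** The week-6 visit "Marks the end of doing acupressure and the beginning of the follow-up phase"; women in the acupressure arms are told that "they are asked to stop acupressure treatment for the next 4 weeks".
- **Recall period.** "The PSQI evaluates sleep disturbance over the past month". The week-6 score therefore reflects time on treatment and the week-10 score time off it.

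The article does not say whether baseline PSQI is a covariate or an outcome row. The BFI framework points to a covariate.

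**The concern.** The aim asks what six weeks of acupressure does to sleep. The interaction that the framework puts first answers another question once it is moved to PSQI. The BFI has two on-treatment phases, so its interaction carries some information on how benefit builds up. The PSQI has a single on-treatment score after baseline, followed by one score four weeks after stopping. A slope between those two describes persistence or relapse.

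At stake is the stated test for the lead sleep outcome. A lasting benefit would tend to give a non-significant interaction, and a benefit that wears off would tend to give a significant one pointing towards worse sleep in the treated arms. Read as the BFI paragraph reads its interaction, as a difference in the extent of decrease, either result would mislead.

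**Working it through.** **Inputs from the article.** 100 women per arm; 5% level; intra-subject correlation 0.5; PSQI means at end of treatment 7, 6, 5 (standard of care, SA, RA).

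**Assumptions.** All arms start at 7. A fraction r of each arm's benefit remains at week 10. The PSQI standard deviation (SD) is 2 to 3.76. The article gives ± 0.376 and ± 0.325 without saying whether they are SDs or standard errors; 3.76 is what 0.376 would imply as a standard error from 100 women. Powers use the noncentral F with λ = n × Σ(arm value − mean of arms)² / variance.

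**The article's own figure.** The Power analysis section claims more than 99% power for group, phase and group*phase. It assumes that "The mean PSQI values at mid-treatment are assumed to be 7, 6, 6, respectively in standard care, SA and RA arms", then 7, 6, 5 at end of treatment.
- The arm changes are 0, 0, −1, so Σ = 2/3. The variance of a change is 2 × SD² × (1 − 0.5) = SD², and λ = 66.7/SD².
- With 0.376 taken as the SD, power is 1.000 for all three effects, so the claim reproduces.
- With SD 2, 2.5 or 3, group*phase power is 0.96, 0.84 or 0.68.
- Whatever the SD, this design has a mid-treatment and an end-treatment score. No mid-treatment PSQI is scheduled, so the claim does not belong to the planned week model.

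**Reading A: baseline is a covariate, outcomes at weeks 6 and 10.** Let d6 and d10 be the RA minus standard-of-care differences: d6 = −2, d10 = −2r. The group*week coefficient is (d10 − d6)/4. With week entered uncentred, the group coefficient is d6 − 6 × slope, the difference extrapolated to week 0.

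| r | slope per week | group coefficient (week 0) | true week-6 difference | group*week power, SD 2 to 3.76 |
|---|---|---|---|---|
| 0 | (0 + 2)/4 = +0.50 | −2 − 3 = −5.0 | −2 | 1.00 to 0.93 |
| 0.5 | (−1 + 2)/4 = +0.25 | −2 − 1.5 = −3.5 | −2 | 0.89 to 0.37 |
| 1 | 0 | −2.0 | −2 | 0.05 |

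The λ values are 200/SD², 50/SD² and 0. The power in the first two rows is power to detect loss of benefit.

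A line through two times is saturated. In simulation, continuous and categorical week gave the same residual sum of squares and the same week-6 difference. Two other quantities remain available from the model:
- Week-6 three-arm test, variance 0.75 SD², λ = 266.7/SD²: power 1.00 to 0.98 for every r.
- Group effect averaged over both visits, variance SD² × (0.75 − 0.25) = 0.5 SD². At r = 1, λ = 400/SD² and power is above 0.99. At r = 0, λ = 100/SD² and power is 1.00 to 0.66.

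**Reading B: baseline is an outcome row, with a line through weeks 0, 6 and 10.** Mean week 5.33; sum of squared deviations 50.67; RA minus standard of care is 0, −2, −2r.

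| r | mean | slope | fitted week-6 difference | share of −2 | group*week power, SD 2 to 3.76 |
|---|---|---|---|---|---|
| 0 | −0.667 | −1.333/50.67 = −0.026 | −0.667 − 0.667 × 0.026 = −0.68 | 34% | 0.12 to 0.07 |
| 0.5 | −1.000 | −6.000/50.67 = −0.118 | −1.000 − 0.667 × 0.118 = −1.08 | 54% | 0.97 to 0.50 |
| 1 | −1.333 | −10.667/50.67 = −0.211 | −1.333 − 0.667 × 0.211 = −1.47 | 74% | 1.00 to 0.95 |

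**Which r is plausible?** The article gives no week-10 PSQI means. For the BFI it assumes 4, 3, 2 at end of treatment and 5, 4, 3 at washout, so the differences between arms do not change. If PSQI behaved likewise, group*week in reading A would be exactly zero. For that BFI comparison the article claims power for phase and group effects only, not for the interaction.

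**The case against.** The strongest reply is that the continuous week term does no harm in the reading the text best supports. With only weeks 6 and 10 as outcomes, making visit categorical re-expresses the same model, and its interaction has the same 5% rejection rate under a sustained benefit. The weakness comes from the interaction taken over from the BFI model. The power section also lists the group effect for PSQI, so a reader of the results would not look at the slope alone. All of this stands. One qualification: with raw week beside group*week, the group coefficient is the week-0 extrapolation, not the average over visits, so the useful group effect has to be asked for.

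Three stronger readings are tempting and unsupported.
- **That a linear week term misses the treatment effect.** In reading A nothing is lost; in reading B the effect is attenuated.
- **That only about 8% of the effect survives.** That comes from slope × 6 in reading B with all benefit lost (0.0263 × 6 = 0.16 of 2). It ignores the group term, takes the most unfavourable persistence, and makes baseline an outcome row, contrary to the BFI framework. The fitted week-6 difference in that same case is 34%.
- **That the PSQI > 7 logistic model has the same fault.** The article states no time term for it.

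The analysis plan is not shown, and centring or named contrasts may be settled there. The point does not rest on their absence: the article itself states the time term and, through the BFI framework, the test of main interest.

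**Conclusion.** The concern holds in a limited form. Read with the BFI framework, the stated PSQI test is a test of off-treatment change and does not address the six-week aim. For a sustained 2-point benefit it rejects 5% of the time, while the week-6 three-arm test on the same data has power 0.98 to 1.00. If baseline PSQI is an outcome row, the week-6 difference is recovered to 34% to 74%, depending on persistence.

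The slopes, extrapolated coefficients and percentages follow from the visit times, the article's 7, 6, 5 means, equal baselines and the assumed r; they do not depend on the SD. The powers also depend on the assumed SD of 2 to 3.76. That the interaction is primary for PSQI is inferred from the statement that its analysis will be similar to that for the BFI.

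This concerns the lead outcome of a secondary aim. The primary BFI analysis uses categorical phases and is not affected, so the point deserves correction but does not threaten the trial's main conclusion.

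**What to change.** - State that baseline PSQI is a covariate, and that the outcomes are weeks 6 and 10.
- Enter visit as a two-level factor with group*visit. This leaves the fit unchanged but removes the extrapolated group coefficient and rules out reading B.
- Name the week-6 differences, RA vs standard of care and RA vs SA, as the target contrasts. Report the same differences at week 10 as the durability contrasts, and do not use the interaction as the test of benefit.
- If the PSQI > 7 model uses repeated visits, give it the same contrasts.

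The cost is a few lines of specification: no extra data, and no extra parameters when baseline is a covariate.

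The power statement should follow the contrasts. The 0.98 to 1.00 above is for the three-arm test. The RA vs SA difference at week 6 is 1 point under the article's means. With variance 0.75 SD² per woman its standard error is √(2 × 0.75 × SD²/100), which is 0.245, 0.306, 0.367 or 0.461 at SD 2, 2.5, 3 or 3.76. The two-sided 5% power is then about 0.98, 0.90, 0.77 or 0.58, before any multiplicity adjustment, so the SD needs to be stated.

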Two types of fatigue-related measures will be collected from the Actiwatch-S. The first is a daytime activity count per minute, which is calculated by dividing the total daily activity counts by the total daytime minutes. For each phase as defined above, we shall use the corresponding 21-day (or 28-day) average as appropriate. The second type of measure is obtained from the four self-reported readings of the VAS-F. The daily averages are obtained from the non-missing entries each day, and are then combined to provide the phase average the same way as the daytime activity count. The analytical framework is identical to that for BFI, albeit with the changed outcome.

A secondary analysis with BFI will also be carried out which investigates the difference in proportion of severely fatigued subjects (BFI ≥ 6) across the three study arms. The analytical framework will be that of a mixed-effects logistic regression model with severe BFI (yes/no) being the dichotomous outcome. Apart from group, phase, and group*phase interaction as primary covariates, the model will also be adjusted for baseline status of severity. Remaining covariates in the model are identical to those in the continuous BFI model. The clustering effect due to subject will be accounted for using a generalized estimating equations approach.

In order to assess the extent of association between the improvement in FACT-B and improvement in fatigue measure (specific aim #1 letter D), we shall create the change-scores (week 6 – baseline, week 10 – baseline) for FACT-B (both total and component scores), and BFI. Then we shall fit a linear mixed model similar to that for the original BFI analysis, with BFI change-score as outcome, and the FACT-B change-score as a time-varying covariate. There will not be any phase or week variable in the model. We shall restrict this analysis to the SA and RA arms only so that the group variable will consist of two levels. A group*FACT-B interaction in the model will investigate any differential association across the arms between the change-scores. The additional covariates and clustering adjustment would be similar to the BFI analysis.

Secondary Aims:

1. Assessing difference across study arms with respect to sleep parameters

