For sleep, we shall use the VAS-SQ measure to carry out our time to onset analysis. As in the case of fatigue, a 3-point drop from baseline in VAS-SQ for the first time will be considered as onset. Since the VAS-SQ measures are weekly, we shall employ a *discrete survival analysis* technique to analyze this data. A discrete survival model is a logistic regression model of the discrete-time hazards, and is easily implemented in most standard statistical softwares. As in the case for VAS-F, this analysis will be confined to subjects with a baseline VAS-SQ score of 3 or more.

We would analyze similarly the time to relapse since the end of treatment, which is defined as the first time a 3-point increase (VAS-F or VAS-SQ) from the six-week value, occurs. This part of the analysis will be restricted to subjects for whom an onset has occurred.

All statistical analyses will be carried out in SAS 9.3 and PASW version 19.

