Along with numerous strengths our study also has several limitations including inability to double blind the study and lack of an objective measure of fatigue. Currently, there are no biomarkers for measuring fatigue. Consequently, fatigue is measured using subjective questionnaires only. While fatigue is a subjective experience, the presence of high amounts of variability between and within participants’ fatigue, over even a short time frame of a day, argue the benefit of pairing objective measures of fatigue with subjective questionnaires. We have included the objective measurement of physical activity and sleep measures using actigraphy. While actigraphy data does not give an objective measure of fatigue it does give insights into the effect of fatigue on daily activity and sleep. Another limitation is our inability to double-blind the participants as to study assignment. Data from our pilot study
[13] demonstrated that participants were blinded as to the acupressure treatment to which they were randomized. However, this is not the case between women in this study who are randomized to one of the two acupressure arms and the standard of care arm. Despite this limitation, it is an important study design to be able to compare acupressure treatment to standard of care for fatigue in these women. By having this comparison we will be able to have a preliminary idea about the comparative effectiveness of acupressure compared to standard of care and have a clearer idea of what is the placebo versus the real effect of acupressure treatment.

In summary, this is a protocol examining two opposing types of self-administered acupressure (stimulating and relaxing) compared to standard of care for PCRF in 300 BC survivors. This protocol has many strengths compared to the traditional randomized, double-blind design. In particular, it utilizes local community resources in the form of MSU County Extension Services for study visits, population-based recruiting via the MTR, and nurses to teach the acupressure intervention. This study is scheduled to be completed with recruitment in the Winter of 2014 with published results in 2015.

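### Onset is the first single day VAS-F is 3 points below baseline, with no persistence rule and no standard-of-care arm, so day-to-day fluctuation can count as acupressure onset

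*Protocol article*

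**What the plan says.** The last paragraph of Study aims and hypotheses sets a secondary aim: to find how long acupressure takes to produce a clinically meaningful effect, and how long that effect lasts after stopping. Both are absolute quantities.

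Under Statistics and power analysis, secondary aim 2 sets the rule:

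- The measure: "For fatigue, we shall use the daily average values of VAS-F". Earlier in the same section, "The daily averages are obtained from the non-missing entries each day", so a day may rest on a single reading.
- The event: "Time to onset will be calculated as the first time (in days) the VAS falls down by 3 points in comparison to the baseline". No confirmation or duration is required. Women need a baseline VAS-F of at least 3.
- The arms: "Time to onset of the acupressure effect will be investigated by studying the treatment subgroups, namely RA and SA". The model is proportional hazards: "Treatment arm (RA vs. SA) will be used as the primary covariate in the analysis".
- Relapse is the first 3-point rise from the six-week value. "This part of the analysis will be restricted to subjects for whom an onset has occurred".

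The Discussion remarks on "the presence of high amounts of variability between and within" participants' fatigue, even over one day. It also justifies the standard-of-care arm as helping to tell placebo from real effect.

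**The concern.** A first-crossing event on a daily series can only accumulate. One low day in six weeks counts as onset, and a return to the old level the next day does not undo it. If women's daily averages move appreciably around a steady mean, some will cross the line with no treatment effect.

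The standard-of-care arm could show how often that happens, but this analysis leaves it out. A median onset of, say, two weeks could then reflect treatment, natural fluctuation or both, and the trial would have no means of saying which.

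The problem carries into relapse. A woman with one low day in week 2 who is back at her usual level by week 6 still enters the relapse analysis, although she has no effect left to lose. What is at stake is the onset time and duration of effect meant to guide clinical use.

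**Working it through.** The protocol gives no expected onset rate, event count or power for this analysis, so there is no planned figure to reproduce. The check asks how often a woman whose fatigue does not change would meet the rule.

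**Inputs from the protocol.** 0–10 scale; 3-point drop; baseline VAS-F at least 3; one week of run-in; six weeks of treatment, so 6 × 7 = 42 daily looks.

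**Assumed, because the documents do not say.** The within-woman SD of the daily average (0.75 to 2.0); day-to-day autocorrelation (0 to 0.6); baseline equal to the 7-day run-in mean; women's true means roughly normal around 5.5 with SD 1.5, limited to 3–9; scores limited to 0–10.

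**Step 1, closed form.** With a known baseline and independent days, the chance of a crossing on one day is p = Φ(−3/SD), and over 42 days it is 1 − (1 − p)^42.

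- SD 1.0: p = Φ(−3) = 0.00135, giving 5.5%.
- SD 1.5: p = Φ(−2) = 0.0228, giving 62%.
- SD 2.0: p = Φ(−1.5) = 0.0668, giving 94.5%.

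The result reaches 50% when p = 1 − 0.5^(1/42) = 0.0164, that is at SD = 3/2.14 ≈ 1.4.

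**Step 2, simulation.** 40,000 women per setting, first-order autoregressive noise, no true change. Ranges run over autocorrelation 0 to 0.6.

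| Assumed SD | Closed form | Single-day rule as written | Trailing 7-day mean |
|---|---|---|---|
| 0.75 | 0.1% | 0.4–1.2% | 0% |
| 1.0 | 5.5% | 9–13% | 0–0.6% |
| 1.25 | 29% | 34–36% | 0–3.6% |
| 1.5 | 62% | 54–62% | 0.1–9.3% |
| 2.0 | 94.5% | 78–89% | 2.3–25% |

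Other modelling choices the documents leave open move the single-day figures by a few points. Allowing for that, I carry forward about 1%, 9–13%, 51–62% and 73–89% at SD 0.75, 1.0, 1.5 and 2.0. If baseline were one day instead of the run-in mean, the rates would be 4–5%, 21–25%, 56–62% and 77–82%.

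**Step 3, what the false onsets look like.** Their median day is about 13–14 at SD 1.5 and 8–9 at SD 2.0, which would look like a credible treatment response. A lasting true fall of only 1 point would still be recorded as a 3-point onset in 59% of women at SD 1.0 and 90% at SD 1.5 (autocorrelation 0.3).

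**Step 4, relapse.** If the six-week value were one day's score, with a steady mean of 4 and independent days, a 3-point rise would occur by chance within 28 days in 19%, 50% and 67% of women at SD 1.0, 1.5 and 2.0. The article does not say whether that value is one day or an average, so these figures hold only under the one-day reading.

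**The case against.** The strongest reply is that the planned inference compares RA with SA. Both arms are randomised and follow the same rule, so chance crossings and regression to the mean fall on both and mainly pull the hazard ratio towards 1. They do not create a false difference. VAS-F against standard of care is also analysed elsewhere, through phase averages in all three arms. This stands. It protects the comparison, but not the absolute onset time that the aim asks for.

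A reader might go further and infer that most recorded onsets would be noise. The documents do not support that. They give no day-to-day SD, and a majority of unchanged women cross only at an SD of about 1.4 or more. Even then, the chance of crossing without an effect is not the share of observed onsets that are false; that also depends on how many women truly respond. The Discussion's remark covers fluctuation within a day, which averaging up to four readings dampens. The power section implies a within-subject SD of 2 (subject variance 4, intra-class correlation 0.5), but for phase-level BFI.

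A reader might also infer that a 3-point drop exceeds the planned benefit, since the power section puts RA 2 points below standard of care (4 versus 2). That compares a between-arm BFI difference with a within-woman VAS-F fall. From an assumed baseline of 5, the RA mean of 2 would itself be a 3-point fall, and the reduction of up to 70% cited in the Background would be 0.7 × 5 = 3.5 points. The threshold is not at odds with the plan.

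How baseline and the six-week value are averaged may fairly be left to a fuller document. The first-crossing rule, the choice of arms and the entry condition for relapse are stated in the article.

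**Conclusion.** The point holds as a limit on interpreting one secondary analysis. The single-day rule can count ordinary fluctuation as onset, and without standard of care the background rate cannot be separated from an acupressure effect. The absolute time to onset is therefore not identified.

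The size rests entirely on an SD the documents do not give: negligible at 0.75, about one unchanged woman in ten at 1.0, more than half at 1.5, and roughly three-quarters or more at 2.0. These figures assume a 7-day-mean baseline and autocorrelation of 0 to 0.6. The entry condition for relapse is loose whatever the SD.

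This is worth changing because it is cheap, but it does not threaten the trial's main conclusion.

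**What to change.** - **Onset.** Define it as the first day on which the trailing 7-day mean VAS-F is at least 3 points below the 7-day run-in mean, keeping the protocol's own threshold. Retain the single-day rule as a sensitivity analysis, because the Discussion also asks whether effects are sudden or cumulative.
- **Background rate.** Apply the same rule to the standard-of-care arm and report its crossing rate beside RA and SA. Table 2 schedules daily Actiwatch data from day −7 to 70 and exempts that arm only from performing acupressure.
- **Readings.** Use only the three scheduled daily readings. Run-in has three a day, while the fourth is entered after acupressure, so standard of care has no counterpart to it. Including it would compare averages of different make-up.
- **Relapse.** Restrict the analysis to women still in response at week 6, and measure the 3-point rise in the 7-day mean from the week-6 7-day mean.

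The cost is rewording and reprogramming on data already scheduled. Onset before about day 7 cannot be dated precisely, and abrupt changes are smoothed. False onset is reduced, not removed: it could still reach about a quarter of unchanged women at SD 2.0 with autocorrelation 0.6, which is another reason to show the standard-of-care rate.
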